# Evaluation of microvascular endothelial function in patients with infective endocarditis using laser speckle contrast imaging and skin video-capillaroscopy: research proposal of a case control prospective study

**DOI:** 10.1186/s13104-017-2660-3

**Published:** 2017-07-28

**Keywords:** Infective endocarditis, Microcirculation, Microvascular dysfunction, Speckle contrast imaging, Skin video-capillaroscopy

## Abstract

**Objective:**

Infective endocarditis is a severe condition with high in-hospital and 5-year mortality. There is increasing incidence of infective endocarditis, which may be related to healthcare and changes in prophylaxis recommendations regarding oral procedures. Few studies have evaluated the microcirculation in patients with infective endocarditis, and so far, none have utilized laser-based technology or evaluated functional capillary density. The aim of the study is to evaluate the changes in the systemic microvascular bed of patients with both acute and subacute endocarditis. This is a cohort study that will include adult patients with confirmed active infective endocarditis according to the modified Duke criteria who were admitted to our center for treatment. A control group of sex- and age-matched healthy volunteers will be included. Functional capillary density, which is defined as the number of spontaneously perfused capillaries per square millimeter of skin, will be assessed by video-microscopy with an epi-illuminated fiber optic microscope. Capillary recruitment will be evaluated using post-occlusive reactive hyperemia. Microvascular flow will be evaluated in the forearm using a laser speckle contrast imaging system for the noninvasive and continuous measurement of cutaneous microvascular perfusion changes. Laser speckle contrast imaging will be used in combination with skin iontophoresis of acetylcholine, an endothelium-dependent vasodilator, or sodium nitroprusside (endothelium independent) to test microvascular reactivity.

**Results:**

The present study will contribute to the investigation of microcirculatory changes in infective endocarditis and possibly lead to an earlier diagnosis of the condition and/or determination of its severity and complications.

*Trial registration* ClinicalTrials.gov ID: NCT02940340.

## Introduction

Infective endocarditis (IE) is a disease with a high mortality rate that can potentially lead to severe complications. Its clinical presentation is dynamic and variable; it is dependent on patient age, the presence of comorbidities (especially underlying valvular heart disease), the causative microorganism and the presence of complications. In recent years, there has been a change in its epidemiological profile, especially in developed countries. Although younger patients with rheumatic valve disease were the predominant population affected by IE, in the last two decades, older individuals and healthcare-associated infections (including those related to intracardiac devices, valve prosthesis and hemodialysis) and a staphylococcal etiology have become more frequent [1, 2]. However, in developing countries, patients with rheumatic valve disease account for a third of all IE cases, and the *viridans* group streptococci is the causative agent in a third of all IE cases [3].

Infective endocarditis is a systemic disease involving the vascular system and is often accompanied by bacteremia or fungaemia. Therefore, it results in a septic state. In addition, acute heart failure or acute-on-chronic heart failure commonly complicates left-sided IE due to valve destruction, which leads to acute valvular regurgitation. Indeed, the most common indication for valve replacement surgery is severe heart dysfunction not amenable to pharmacologic intervention [1–3]. Considering the severity and increasing incidence of IE, it is important to better understand the pathophysiology of the endocarditis syndrome. The use of noninvasive techniques in the early diagnosis of IE and its complications may prove useful. In fact, the evaluation of systemic microvascular reactivity has proven to be very helpful in the investigation of the pathophysiology of cardiovascular and metabolic disorders [4, 5] as well as sepsis [6].

Abnormalities in the microcirculation have been demonstrated through microvascular rarefaction to be present in diseases such as arterial hypertension, diabetes, obesity and metabolic syndrome [5, 7–11]. Moreover, impaired systemic microvascular function, characterized primarily by capillary rarefaction in the skin, has been demonstrated in individuals with increased coronary artery disease risk [12, 13].

The importance of vascular endothelial function in cardiovascular medicine has also been demonstrated using microRNAs (miRs), non-coding RNAs that can regulate gene expression via translational repression and/or post-transcriptional degradation [14]. One of the examples is miR-126, which plays a fundamental role in homeostasis and in the modulation of vascular development. Endothelial function can also be regulated by miRs commonly expressed in endothelial cells. One of the best examples of this is miR-223, a cholesterol homeostasis regulator [14].

Laser speckle contrast imaging, which is used to assess skin microvascular reactivity, allows for innovative and reproducible noninvasive evaluation of tissue flow with high real-time spatial resolution in patients with cardiometabolic diseases [15, 16] and critically ill patients [17, 18]. Moreover, cutaneous microvascular reactivity has been correlated to microvascular function in different vascular beds, both in intensity and regarding the underlying mechanisms [19].

Although IE is the prototype of a septic condition that results in acute heart dysfunction, only one study has addressed microcirculation in infective endocarditis [20], and thus far, none have utilized laser speckle contrast imaging or functional skin video-capillaroscopy. Studies have shown microvascular changes in sepsis, in which abnormalities are found in early phases even before the deterioration of hemodynamic parameters [21]. These studies show the relationship of microcirculatory changes with organ failure and mortality, which are independent of the systemic hemodynamic variables [21]. It is probable that in acute staphylococcal endocarditis, findings similar to those in the studied sepsis models may be encountered [17, 22].

The goal of this study is to assess microvascular density and reactivity in patients with acute and subacute endocarditis by laser speckle contrast imaging and skin video-capillaroscopy.

## Main text

### Methods

#### Study design and place

This is a cohort study that will include patients with a confirmed diagnosis of infective endocarditis who were admitted to the National Institute of Cardiology (NIC) at the Ministry of Health in Rio de Janeiro, Brazil. The NIC is a national reference center for the treatment and research of cardiovascular diseases. Its staff is composed of cardiologists, cardiothoracic surgeons, infectious diseases specialists, specialized nursing staff, physiotherapists and pharmacists as well as technical staff. The investigative resources include echocardiography, computed tomography, magnetic resonance imaging and scintigraphy. The NIC has outpatient units, four intensive care units and operating theatres where approximately 1300 cardiac surgeries are performed yearly.

#### Study participants and recruitment

Patients will be recruited consecutively and prospectively from the endocarditis cohort. The eligibility criteria are as follows: (1) confirmed IE according to the modified Duke criteria [23]; (2) inpatient treatment at the NIC; (3) clinical stability as evaluated by the investigator; and (4) age ≥ 18 years. The exclusion criterion is a confirmed previous diagnosis of *diabetes mellitus*.

#### Study variables

The variables to be included are as follows: demographic data (sex, age and ethnicity), previous medical history (comorbidities, previous valvular diseases and cardiac interventions), medications in use, data regarding the episode of IE (date of onset, causative pathogen, affected valve or structure, echocardiographic data, local and systemic embolic and non-embolic complications, antibiotic and surgical treatment) and laboratory data (CRP, ESR and creatinine levels).

#### Intervention

The evaluation of microvascular endothelial function in patients with infective endocarditis will be performed using laser speckle contrast imaging and skin video-capillaroscopy. These results will be compared to those previously obtained from age- and sex-matched healthy volunteers [13]. The systemic microvascular data obtained from this group of healthy volunteers will be used as reference microcirculatory values of individuals free of systemic diseases. None of the healthy volunteers presented with arterial hypertension, diabetes, dyslipidemia or any other systemic pathology.

#### Evaluation of microcirculatory reactivity

The microcirculatory tests will be performed in the morning between 8 a.m. and 12 p.m. in an undisturbed, quiet room with a defined stable temperature (23 ± 1 °C) following a 20-min rest period in the supine position. The room temperature will be monitored and adjusted if necessary using air conditioning. The acclimatization period will last until each patient’s skin temperature stabilizes [24]. We have previously demonstrated that following 15–20 min of acclimatization, the skin temperature stabilizes at approximately 29 °C [8].

#### Evaluation of skin microvascular flow and reactivity

Microvascular reactivity will be evaluated using a laser speckle contrast imaging (LSCI) system with a laser wavelength of 785 nm (PeriCam PSI system, Perimed, Järfälla, Sweden), as previously described [25]. LSCI will be used in combination with the iontophoresis of acetylcholine (ACh) or sodium nitroprusside (SNP) for the non-invasive, continuous measurement of cutaneous microvascular perfusion changes in arbitrary perfusion units (APUs). The images will be analyzed using the manufacturer’s software (PIMSoft, Perimed, Järfälla, Sweden). One skin site on the ventral surface of the forearm will be randomly chosen for the recordings. Hair, broken skin, areas of skin pigmentation and visible veins will be avoided, and a single drug-delivery electrode will be installed using adhesive discs (LI 611, Perimed, Järfälla, Sweden). A vacuum cushion (AB Germa, Kristianstad, Sweden) will be used to reduce the recording artifacts generated by arm movements. The iontophoresis of ACh 2% w/v or SNP 2% w/v (Sigma Chemical CO, USA) will be performed using a micropharmacology system (PF 751 PeriIont USB Power Supply, Perimed, Sweden) with increasing anodal currents of 30, 60, 90, 120, 150 and 180 μA for 10-s intervals that are spaced 1 min apart, and the total charges will be 0.3, 0.6, 0.9, 1.2, 1.5 and 1.8 mC. The dispersive electrode will be attached approximately 15 cm away from the iontophoresis chamber. The results of the pharmacological tests will be expressed both as peak values (representing the maximal vasodilation observed following the highest dose of ACh or SNP) and as the area under the curve of vasodilation. The measurements of skin blood flow will be divided by mean arterial pressure values to provide the cutaneous vascular conductance (CVC) in APUs/mmHg.

Microvascular reactivity will also be evaluated using a physiological test known as post-occlusive reactive hyperemia (PORH). During the PORH test, arterial occlusion will be achieved with supra-systolic pressure (50 mmHg above the systolic arterial pressure) using a sphygmomanometer for 3 min. Following the release of pressure, maximum flux will be measured.

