In sepsis, microvascular blood flow is disturbed by endothelial dysfunction, which leads to a reduction in flow or no flow at all to some capillary beds, while other beds have above normal flow, even surpassing tissue metabolic demands. This microvascular perfusion heterogeneity results in tissue hypoxia. Endothelial dysfunction in sepsis also results in an inflammatory response, which together with tissue hypoxia, leads to organ failure and mortality [31, 33]. Intravenous fluids and vasoactive agents are important measures in the treatment of sepsis. Intravenous fluids may improve microvascular perfusion, increasing the proportion of perfused capillaries and decreasing flow heterogeneity. However, systemic circulatory changes may be relatively independent of changes in the microcirculation [33, 34].

Our study proposes to evaluate the baseline cutaneous functional capillary density and capillary recruitment (capillary reserve) in patients with IE using PORH. Capillary rarefaction and heterogeneous capillary flow may be shown [18]. In addition to using a laser speckle contrast imaging system, whether microvascular reactivity is normal may be demonstrated with acetylcholine, an endothelium-dependent vasodilator, and sodium nitroprusside, an endothelium-independent vasodilator drug. The results of these studies may be helpful in providing information on the systemic involvement of microcirculation in infective endocarditis.

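### One anodal polarity is stated for both acetylcholine and nitroprusside, although their active ions carry opposite charge, so the SNP test as written is an unreliable endothelium-independent control

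*Protocol article*

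**What the plan says.** In the protocol article, section *Evaluation of skin microvascular flow and reactivity*, both test drugs share one description: "The iontophoresis of ACh 2% w/v or SNP 2% w/v (Sigma Chemical CO, USA) will be performed using a micropharmacology system", and the same sentence continues "with increasing anodal currents of 30, 60, 90, 120, 150 and 180" μA, "for 10-s intervals that are spaced 1 min apart". The charges follow: "the total charges will be 0.3, 0.6, 0.9, 1.2, 1.5 and 1.8 mC". On the hardware, the section says "a single drug-delivery electrode will be installed using adhesive discs". Neither this section nor any other gives a second polarity, or a change of polarity, for SNP.

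For either drug, the response is summarised as a peak after the highest dose and as an area under the curve. The Abstract and the Discussion set the two drugs side by side by mechanism: "acetylcholine, an endothelium-dependent vasodilator, and sodium nitroprusside, an endothelium-independent vasodilator drug". The section *Intervention* compares patients with values obtained earlier in healthy volunteers and does not describe how those volunteers were tested.

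**The concern.** Iontophoresis moves an ion into the skin by repelling it from an electrode of the same sign. Acetylcholine is a quaternary ammonium cation, so an anode drives it. In a sodium salt the sodium is the cation, so the nitroprusside part, which is the vasodilator, is the anion. An anode repels the sodium and holds the nitroprusside back. The stated polarity therefore suits one drug and not the other.

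What is at stake is the reading of the ACh result. A blunted ACh response points to the endothelium only if the smooth muscle is shown to respond normally to a drug that bypasses the endothelium, and SNP is the only such drug in this study. If SNP does not reach the tissue as intended, a weak SNP response may reflect delivery and not smooth-muscle dysfunction. An ACh deficit could then be wrongly put down to a general failure to dilate.

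**Working it through.** **Inputs.** From *Evaluation of skin microvascular flow and reactivity*: six current steps, 10 s each, anodal, common to both drugs, and six stated charges. From the names of the drugs and basic chemistry, not from the documents: the sign of each active ion.

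**Step 1: reproduce the plan's own figures.** Charge = current × time.

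| Current (μA) | × 10 s (mC) | Stated (mC) |
|---|---|---|
| 30 | 0.3 | 0.3 |
| 60 | 0.6 | 0.6 |
| 90 | 0.9 | 0.9 |
| 120 | 1.2 | 1.2 |
| 150 | 1.5 | 1.5 |
| 180 | 1.8 | 1.8 |

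All six agree. They are charges per step; the sum over the series is 0.3 + 0.6 + 0.9 + 1.2 + 1.5 + 1.8 = 6.3 mC.

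**Step 2: what the charges can show.** Charge is the size of the current multiplied by time. It is the same at either polarity, so these figures neither reveal nor exclude an error of polarity.

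**Step 3: set polarity against ion.**

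| Drug | Active ion | Stated polarity | Active ion driven into the skin by repulsion? |
|---|---|---|---|
| ACh | cation | anodal | yes |
| SNP | anion | anodal (same sentence) | no |

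**Step 4: consequence for the dose scale.** The section treats rising current as rising dose for both drugs. For ACh at the anode this holds. For SNP at the anode, more current does not drive in more nitroprusside by repulsion, so the current steps are not a dose scale. The SNP peak and area under the curve then rest on whatever arrives by passive diffusion or solvent flow, plus any response to the current itself. The documents quantify none of these, so no percentage loss can be computed.

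**Step 5: what is untouched.** The sample size rests on capillary density during post-occlusive reactive hyperemia: n = 7.9 × 2 × 7² / 7² = 15.8, rounded up to the stated 16 per group. Iontophoresis does not enter it. Capillaroscopy, the hyperemia test measured by laser speckle imaging, and the ACh test do not depend on how SNP is delivered.

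**The case against.** The best counter-argument is that this is a drafting slip. The article is condensed, its laser speckle method is referred to an earlier publication, and one adjective in a joint clause on ACh or SNP could easily come from merging two procedures. The practice may be correct. That stands as a possibility, and it lowers the likely harm. It does not remove the point: the article does not leave polarity to a fuller document but states it, for both drugs, and anyone following the text would apply the wrong setting to one of them.

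It can also be said that the test is secondary. This is largely fair. The only powered comparison is capillary density, and *Statistical analysis* names no contrast of ACh with SNP. The control role of SNP comes from the way the Abstract and the Discussion pair the two drugs. Yet the study's title is about endothelial function, and the Discussion expects the pair to show "whether microvascular reactivity is normal may be demonstrated with acetylcholine, an endothelium-dependent vasodilator, and sodium nitroprusside, an endothelium-independent vasodilator drug". That use needs a sound SNP test.

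A reader might go further and infer that no SNP would be delivered and that its results would mean nothing. The documents do not support this: diffusion and solvent flow may carry some drug, and the amount is unknown. A reader might also infer that patients will show a false deficit against the volunteers. That would require the volunteers to have received SNP at a different polarity. The article states neither their polarity nor that SNP data exist for them. If the same setting was used, the comparison between groups is like for like, although SNP would remain a weak control.

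**Conclusion.** The point holds as an error in a stated measurement rule. One anodal setting cannot electrically drive both a cation and an anion, so as written the SNP peak and area under the curve cannot be relied on as the endothelium-independent test. All six SNP current steps are affected wherever the text is followed literally.

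The size of the distortion cannot be derived from the documents. The conclusion rests on two things: the sign of each active ion, which is basic chemistry, and the assumption that the sentence means what it says for both drugs. Any bias against the volunteers is conditional on a polarity that the article does not give. SNP is a test applied to participants and not an allocated arm, so no group of participants is lost. The sample size calculation and the results of the other tests stand.

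**What to change.** In *Evaluation of skin microvascular flow and reactivity*, state the polarity separately for ACh and for SNP, each consistent with the charge of its active ion. Reconcile the wording with the method the article cites as previously described, with what is done in practice, and with the method used in the reference volunteers.

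Then add one conditional rule: if SNP data exist for the volunteers and were obtained at a different polarity from the patients' data, they are not used as the SNP reference. If any patients have already been tested, record the polarity actually used, so that their SNP results can be interpreted or set aside.

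The change to the text is about one sentence plus the conditional rule, and the rest is a check of laboratory records. No sample size, power or significance level changes. If the practice already differs from the text, only the text needs correcting.

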#### Capillaroscopy by intra-vital video-microscopy

Capillary density, i.e., the number of perfused capillaries per mm^2^ of skin area, will be assessed by high-resolution intra-vital color microscopy (Moritex, Cambridge, UK), as previously described [8]. Capillaroscopy will be performed using a video microscopy system with an epi-illuminated fiber optic microscope containing a 100-W mercury vapor lamp light source and an M200 objective with a final magnification of 200×. The dorsum of the non-dominant middle phalanx will be used for image acquisition, which will occur while the patient is seated comfortably in a constant temperature environment (23 ± 1 °C). Images will be acquired and saved for subsequent offline analysis using a semi-automatic integrated system (Microvision Instruments, Evry, France). Mean capillary density will be calculated as the arithmetic mean of the number of visible (i.e., spontaneously perfused) capillaries in three contiguous microscopic fields of 1 mm^2^ each. A blood pressure cuff will then be applied to the patient’s arm and inflated to supra-systolic pressure (50 mmHg above the measured systolic arterial pressure) to interrupt blood flow completely for three minutes. After cuff release, images will again be acquired and recorded for 60–90 s, during which a maximal hyperemic response is expected to occur [26–28]. All images will be analyzed by two independent observers who will have no knowledge of the subject’s group assignment (control subjects or patients).

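### Image reading is described as masked to group, but the controls are reused earlier results, so as written only patient images remain to be read and the masking does not protect the powered comparison

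*Protocol article*

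**What the plan says.** Four parts of the Protocol article bear on this point.

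- **Capillaroscopy by intra-vital video-microscopy.** On acquisition: "Images will be acquired and saved for subsequent offline analysis using a semi-automatic integrated system". On reading: "All images will be analyzed by two independent observers who will have no knowledge of the" subject's group, with control subjects and patients both named.
- **Intervention.** On the source of the controls: "These results will be compared to those previously obtained from age- and sex-matched healthy volunteers", with a citation to an earlier study. On their use: "The systemic microvascular data obtained from this group of healthy volunteers will be used as reference microcirculatory values of individuals free of systemic diseases".
- **Study participants and recruitment.** "Patients will be recruited consecutively and prospectively from the endocarditis cohort". No recruitment of controls is described.
- **Abstract.** "A control group of sex- and age-matched healthy volunteers will be included", which reads as though controls will be enrolled alongside the patients.

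The Sample size calculations section powers the study on capillaries/mm² during PORH, which is the quantity that the two observers count.

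**The concern.** Masking readers to group works only if images from both groups are in the set being read. The Intervention section reuses results and data that already exist, and the recruitment section adds patients only. Taken together, they leave a reading set made up of patients, so a promise that readers do not know the group gives no protection.

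Group then also coincides with reading period: every control value comes from the earlier reading and every patient value from the new one. The count comes from a semi-automatic system, so some human judgement enters. If the threshold for counting a capillary as perfused differs between the two periods, that difference is added in full to the estimated effect of endocarditis. No covariate can separate group from period. A larger sample would only estimate the shifted difference more precisely.

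The Limitations and strengths section names the small number of patients and their heterogeneity, but not the historical control. A reader of the results would therefore credit the main comparison with masked assessment that the described design does not deliver.

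**Working it through.** **Step 1. Set the sections side by side.**

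| Question | What the article gives | Section |
|---|---|---|
| Who is newly enrolled? | Patients only | Study participants and recruitment |
| Where do control values come from? | Results of an earlier, cited study | Intervention |
| How are they used? | As existing reference data | Intervention |
| Who reads images, and how? | Two observers, masked to group, all images | Capillaroscopy |
| Are archived control images re-read? | Not stated anywhere | – |

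The masking statement has practical content only if the answer in the last row is yes. The Intervention section, which speaks of reusing results and data, points the other way.

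**Step 2. Reproduce the plan's own figure.** Inputs from Sample size calculations: difference δ = 7 capillaries/mm², SD s = 7, f(α, β) = 7.9, 5% significance, 80% power. From Statistical analysis: two-tailed unpaired t-test.

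n = 7.9 × 2 × 7² / 7² = 15.8, rounded up to 16 per group. The stated figure reproduces. Power at 16 per group is 80.7% by the normal approximation and 78.1% by the noncentral t. Nothing here depends on the masking question.

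**Step 3. Illustrate what a reading shift would do.** The documents give no size for a shift, so b below is an assumption, shown over a range.

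- Standard error of the difference: 7 × √(2/16) = 2.475 capillaries/mm².
- Degrees of freedom: 2 × 16 − 2 = 30.
- With no true difference, the test statistic follows a noncentral t with noncentrality b / 2.475. The false-positive rate is the probability that it falls beyond the two-sided 5% limits.
- With a true difference of 7 and a shift against it, the noncentrality is (7 − b) / 2.475.

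| Assumed shift b (capillaries/mm²) | b / 2.475 | False-positive rate, no true difference | Power for a true difference of 7, shift opposing |
|---|---|---|---|
| 0 | 0 | 5.0% | 78% |
| 1 | 0.40 | 6.8% | 65% |
| 2 | 0.81 | 12.3% | 50% |
| 3 | 1.21 | 21.7% | 35% |

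As a share of the planned difference, these shifts are 1/7 = 14%, 2/7 = 29% and 3/7 = 43%. The error can go either way: a shift may create a difference or hide one.

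**The case against.** The best reply is that the masking sentence covers all images and names both groups, and that images are saved for offline reading. Archived control recordings could be coded and mixed in, and the sentence would then be true. A condensed article may also leave such handling to the full protocol. This shows that the problem can be cured, not that the article already cures it. A re-read is stated nowhere and sits badly with the reuse of results previously obtained. The conflict is between two statements in the article, not a detail left out.

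Other parts of the reply do stand, and they limit the point. A reader might infer the following, none of which the documents support:

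- **That a different person read the control images.** The article does not say who read them. It refers to previous work by the same group, so continuity of readers is also possible.
- **That the observers are known to be aware of each subject's status.** The article does not say what they will be told. The point is only that masking has no force when a single group is being read.
- **That bias has been shown.** Drift is a risk that the design cannot exclude. The semi-automatic system, the two observers and the averaging over three fields may all limit it, and it may be nil.
- **That the laser speckle recordings fall under the same criticism.** The masking statement is made in the capillaroscopy section and concerns its images. The laser speckle section makes no such promise.

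The Abstract's wording could also mean that controls are included in the comparison, and the Intervention section does disclose that their data are earlier ones. On its own the Abstract is a matter of wording.

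**Conclusion.** The point holds as an inconsistency that removes a stated protection from the powered comparison. If the text is followed as written, the newly read capillaroscopy images all come from patients, masking to group is not effective, and any change in counting between the two readings enters the group difference in capillary density during PORH.

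This rests on one assumption: that archived control images are not re-read. That is the natural reading of the Intervention section, and no other section contradicts it expressly. If a masked re-read is in fact intended, stating so settles the masking point.

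The size of any effect cannot be known from the documents. Under the plan's SD of 7 and 16 per group, assumed shifts of 0 to 3 capillaries/mm² take the two-sided false-positive rate from about 5% to about 22%. This shows how sensitive the comparison is and does not estimate the bias. The sample size of 16 per group is unaffected.

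**What to change.** State which of the two situations applies, and change the text to match.

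1. **If the control capillaroscopy recordings are stored:** code them, mix them in random order with the patient recordings, have the same two observers read all of them without knowledge of group, and use the re-read control values in the analysis.
2. **If they are not stored:** withdraw the blinding statement and report the comparison as unblinded against historical reference values.

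In either case, make the Abstract say that the controls are historical, and add to the limitations that images were acquired in different periods. A re-read removes reader drift only. It does not remove differences in how images were acquired.

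The cost is some extra reading time for the two observers already planned, plus the wording changes. No new participants are needed. The re-read control values may differ slightly from those obtained earlier, which should be reported openly.
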